# Study protocol of transcranial electrical stimulation at alpha frequency applied during rehabilitation: A randomized controlled trial in chronic stroke patients with visuospatial neglect

**DOI:** 10.1186/s12883-022-02932-7

**Published:** 2022-11-02

**Keywords:** Stroke, Visuospatial neglect, Visual scanning training, Transcranial electrical stimulation, Transcranial alternating current stimulation, Randomized controlled trial, Activities of daily living

## Abstract

**Background:**

A frequent post stroke disorder in lateralized attention is visuospatial neglect (VSN). As VSN has a strong negative impact on recovery in general and independence during daily life, optimal treatment is deemed urgent. Next to traditional stroke treatment, non-invasive brain stimulation offers the potential to facilitate stroke recovery as a complementary approach. In the present study, visual scanning training (VST; the current conventional treatment) will be combined with transcranial alternating current stimulation (tACS) to evaluate the additive effects of repeated sessions of tACS in combination with six-weeks VST rehabilitation.

**Methods:**

In this double-blind randomized placebo-controlled intervention study (RCT), we will compare the effects of active tACS plus VST to sham (placebo) tACS plus VST, both encompassing 18 VST training sessions, 40 minutes each, during 6 weeks. Chronic stroke patients with VSN (> 6 months post-stroke onset) are considered eligible for study participation. In total 22 patients are needed for the study. The primary outcome is change in performance on a cancellation task. Secondary outcomes are changes in performance on a visual detection task, two line bisection tasks, and three measures to assess changes in activities of daily living. Assessment is at baseline, directly after the first and ninth training session, after the last training session (post training), and 1 week and 3 months after termination of the training (follow-up).

**Discussion:**

If effective, a tACS-VST rehabilitation program could be implemented as a treatment option for VSN.

**Trial registration:**

ClinicalTrials.gov; registration number: NCT05466487; registration date: July 18, 2022 retrospectively registered; https://clinicaltrials.gov/ct2/show/NCT05466487

## Background

Visuospatial neglect (VSN) is a common syndrome after unilateral stroke; 25-30% of all stroke patients have VSN [1, 2]. VSN patients show a failure or slowness to report, respond or orient to events and stimuli located in the contralesional side of space [2, 3]. It is thought that the brain damage causes impairment of the brain’s spatial attention mechanisms, resulting in VSN [4, 5]. VSN patients show slower and more attenuated motor recovery patterns [6] and need more help in activities of daily living (ADL) compared to stroke patients without VSN [7]. Moreover, VSN negatively influences participation in society, increases caregiver burden [8] and is negatively related to life satisfaction [9]. These findings show the considerable impact of VSN on daily life and stress the importance of adequate treatment.

Over the past decades, many therapeutic interventions aiming to improve VSN have been developed and evaluated (see for overview [10]) ranging from treatments using top-down strategies such as mental imagery training [11], to bottom-up methods such as prism adaptation [12, 13], and from sustained attention training [14], to non-invasive brain stimulation techniques (NIBS) [15]. Currently, the standard treatment for VSN is a visual scanning training (VST), an intensive compensatory training with emphasis on top-down strategies designed to improve viewing and searching behavior [16]. However, generalization of the effects of VST to everyday life is insufficiently established [10, 17] and there exists a large variability in patients’ benefits from VST [18]. It is unclear why some patients benefit from the training while others do not. One reason could be that top-down methods such as VST may be limited as they solicit the attentional abilities, which may be hampered by lack of awareness of the spatial neglect behavior [10, 18]. The heterogeneity of VSN, with high variability of symptoms within and between patients, may also play a role in the variability of responsiveness to interventions for neglect [12]. Because neglect is a multifaceted disorder, it is suggested that the best treatment might involve a combination of different methods to improve their overall effectiveness [10, 12, 15, 19–21].

NIBS offers a completely different strategy to facilitate recovery, not by means of a behavioral approach submitting the patient to a program of standardized behavioral tasks that require a voluntary (attentional) effort by the patient to follow a therapist’s instructions (such as VST), but by directly inducing neuroplastic changes in the patient’s brain, hoping to positively affect cognitive functioning. For example, brain stimulation protocols can be tuned to modulate oscillatory brain activity (for review see [22]). This is particularly interesting in the field of neglect rehabilitation, as oscillatory activity in the alpha range (8-12 Hz) in posterior parietal cortices has been linked to spatial attention bias in healthy subjects [23–27]. In our recent studies, we showed that transcranial alternating current stimulation (tACS), applied at alpha frequency, can be used to influence visuospatial attention performance in healthy participants [28] and in sub-acute VSN patients [ 29] in a single session.

To our knowledge, no study has yet reported the combined impact of this oscillatory-based NIBS approach and conventional neglect therapy on rehabilitation outcome. The overall aim of the current study is therefore to evaluate the effects of repeated sessions of tACS in combination with six-weeks VST rehabilitation. Our primary research question is: Does VST complemented with active tACS improve neglect-related symptoms to a larger extent compared to VST with sham (placebo) tACS post training compared to baseline? Secondary questions are: 1) whether long-lasting effects occur, 2) whether effects already occur earlier during the six-weeks training, and 3) whether effects generalize to daily-life situations.

## Methods

### Design

This study is a double-blind randomized placebo-controlled intervention study (RCT; Fig. 1). We will compare the effects of active tACS to sham (control) tACS, both combined with conventional rehabilitation (VST). Irrespective of the intervention group, *all* patients will receive VST during the (active or sham) stimulation.

**Fig. 1 Fig1:**
[figure not shown]
Study flow chart

This study is conducted according to the principles of the Declaration of Helsinki (59th WMA General Assembly, Seoul, Korea, October 2008) and in accordance with the Medical Research Involving Human Subjects Act (WMO). The study is approved by the Medical-Ethical Committee azM/UM of Maastricht University (NL70256.068.19 / METC 19-047) and registered in ClinicalTrials.gov (Non-Invasive Brain Stimulation as an Innovative Treatment for Chronic Neglect Patients (NibsNeglect), NCT05466487).

### Patient sample – inclusion and exclusion criteria

Patients with a clinically diagnosed, chronic stroke and with signs of neglect symptoms (based on clinical judgment), will be considered eligible for our study. Patients will be recruited by psychologists of healthcare organizations in The Netherlands that are specialized in supporting and treating people with acquired brain injury (InteraktContour, De Hoogstraat Revalidatie, Heliomare, De Noorderbrug, Esdégé-Reigersdaal). The inclusion of participants started in September 2020 and data will be collected until September 2023.

Inclusion criteria are: 1) neurologically objectified stroke (first or recurrent, ischemic or intracerebral or subarachnoid hemorrhagic lesion; 2) stroke occurred when patient was 18-80 years of age; 3) chronic stroke (> 6 months post-stroke onset); 4) sufficient comprehension and communication skills to benefit from training (based on clinical judgement); and lastly 5) a screening containing four neuropsychological tests will be performed to evaluate the current severity of the neglect, since the diagnosis of neglect may have been established months or even years ago in our sample of chronic stroke patients.

Exclusion criteria are: 1) currently engaging in cognitive rehabilitation treatment or neglect treatment; 2) physically or mentally unable to participate (based on clinical judgment); 3) hemianopsia (based on clinical judgement); 4) severe communicative disability, as task descriptions need to be understood; 5) local scalp injuries; 6) eczema on scalp or psoriasis; 7) diagnosed (neuro) psychiatric or neurodegenerative diseases; 8) current alcohol and/or drug abuse; and 9) pregnancy, due to tACS safety considerations (5-9).

### Procedure, neglect screening, outcome measures, and baseline descriptors

Patients are allowed to proceed in the study when they show neglect on minimally one of the four screening tasks, on the basis of standard norms: bells task (BT) [30], balloons-subtest B (BB) [31], Schenkenberg line bisection task (SLBT) [32], and McIntosh line bisection task (MLBT) [33, 34]. Patients who show neglect during screening will be randomly assigned to either the experimental (active tACS) or placebo (sham tACS) condition, and will receive VST training for six weeks. Enrolled patients will be tested six times on an array of tasks: before the training (T0; baseline), after the first (T1), ninth (T2), and eighteenth (T3) training session, as well as one week (T4) and three months (T5) after termination of the training (Fig. 1). The star cancellation task (SCT), computerized visual detection task (CVDT), MLBT-digitized (MLBT-d), and SLBT will be assessed during all six testing-time points in the study (T0-T5). The baking tray task (BTT), Catherine Bergego scale (CBS), and subjective neglect questionnaire (SNQ) will be administered at four testing-time points (T0, T2, T4, and T5).

#### Screening tasks

##### Bells task (BT)

This cancellation task will be presented on an A4 paper and consists of 35 target items (bells), interspersed among 280 distractor objects [30]. Patients will be instructed to mark all bells. Four or more omissions are considered as indicative for VSN [18].

##### Balloons-subtest B (BB)

The scores of subtest B of the balloons test [31] will be used to calculate a total score (total number of targets cancelled) and a laterality score (number of targets cancelled on the left side of the page expressed as a percentage of the total number of targets cancelled). Subtest B consists of an A3 paper with 20 targets (circles) and 180 distractors (balloons). A total score of less than 17 *and* a laterality score of less than 45% is indicative of left VSN.

##### Schenkenberg line bisection task (SLBT)

The SLBT consists of 20 horizontal lines, varying from 10 to 20 cm in length (average 15 cm), at three different positions (left, middle, right) on a landscape-oriented A4 sheet [32]. Patients will be asked to mark their perceived midpoint of every line. The following formula will be used to calculate the relative deviation score:$$deviation=\frac{\left( bisection\ mark- true\ center\right)}{true\ center}\cdot 100\%$$

Where values are always measured from the left end of the line. The relative deviation scores will then be averaged across all 20 lines to generate the summary score, and across the three line positions to generate the left, middle, and right average score, respectively. VSN is indicated when the average bisection mark deviates more than 10% from the true center [32].

##### McIntosh line bisection task (MLBT)

The MLBT provides a simple measure of lateral asymmetry, the endpoint weightings bias (EWB) [33, 34]. The EWB is a different approach to line bisection to diagnose VSN. Compared to classical line bisection tests, the EWB is a more theoretically neutral and parsimonious approach, based on the weight one distributes to both of the endpoints of the line, rather than using the deviation from the midpoint. The MLBT consists of 32 horizontal lines (width: 3 mm), each presented individually on an A4 sheet. The patient is asked to mark the subjective midpoint of each line. There are eight repetitions of each of four unique lines (lines A, B, C, D), presented in a fixed-random order [33, 34]. We refer to McIntosh and colleagues [33] for the arrangement of the four lines. Each response is coded as a horizontal coordinate relative to the center of the page. The analysis then focuses on how this response position varies from trial-to-trial as a consequence of changes in the left endpoint (lines A & C vs B & D) and changes in the right endpoint (lines A & B vs C & D). Thus, the left endpoint weighting (dPL), the right endpoint weighting (dPR), and the bias towards one of the two endpoints (EWB) are derived as follows:$$dPL=\frac{\left({P}_{mean}\ \textrm{in}\ \textrm{line}\ \textrm{A}\ \textrm{and}\ \textrm{C}\right)-\left({P}_{mean}\ \textrm{in}\ \textrm{line}\ \textrm{B}\ \textrm{and}\ \textrm{D}\right)}{40}$$$$dPR=\frac{\left({P}_{mean}\ \textrm{in}\ \textrm{line}\ \textrm{C}\ \textrm{and}\ \textrm{D}\right)-\left({P}_{mean}\ \textrm{in}\ \textrm{line}\ \textrm{A}\ \textrm{and}\ \textrm{B}\right)}{40}$$$$EWB= dPR- dPL$$

Where dPL and dPR are expressed as a proportion of the endpoint change (40 mm), and range from 0 to 1. Perfect performance would yield symmetrical right and left endpoint weightings of 0.5, and an EWB-value of zero. An EWB-value above zero indicates a greater influence of the right endpoint (over the left), and would be a sign for left sided neglect. To define cut-off scores for the MLBT, we administered the task to healthy controls (*n* = 46, female = 47.7%, age = 57.8 years, SD = 9.2). This yielded a mean EWB of −.0217 (SD = .0546). Scores of 2 SD’s above and below the mean are considered to exceed normal range, leading to upper and lower cut-offs for left and right neglect respectively, of + 0.09 and − 0.13. Study protocol was approved by the ethical committee of the Faculty of Psychology and Neuroscience at Maastricht University (ERCPN number: 177_03_03_2017_S32).

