##### McIntosh line bisection task-digitized (MLBT-d)

A digitized version of the above described MLBT (subsection “Screening tasks”) is also used as study outcome measure. Each of the 32 lines of the MLBT-d are presented individually on a laptop screen. The patient is asked to mark the subjective midpoint of each line by touching the screen with the finger.

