##### Baking tray task (BTT)

The patient is asked to distribute 16 cubes of 3.5 cm as evenly as possible over a 75 × 100 cm board (as if spreading out buns on a baking tray) [39]. The entire board will be scanned using the Microsoft Lens iOS app. Coordinates of all cubes will be manually identified using a custom Python script. An average positive x-coordinate indicates a rightward bias.

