### Statistical analyses

The background characteristics of the patients will be described by using descriptive statistics. Baseline characteristics of the intervention and control group will be compared to detect differences at the start of the trial. Linear mixed model regression analyses with random effects for intercept and slope will be used to test for change in the primary and secondary outcome measures both within and between group. The predictors of theoretical interest are the effects of time and group and the interaction between time and group (fixed effects). Baseline score of the outcome measure, time since stroke, gender, and age will be introduced as potential fixed covariates. This is regardless whether or not these variables differ between groups, to enhance the fit of the model. Post-hoc contrasts will be performed for the interaction between time and group to test differences in treatment effects by intervention group allocation. The intention-to-treat principle is used by including all patients as randomized in the analyses, regardless of whether they received the complete program (dropout, non-adherence). Significance is set to *p* < .05 (two-sided). Analyses will be performed in IBM SPSS Statistics version 26.

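### Three secondary outcomes are signed left-right scores analysed by linear change, with no alignment to lesion side and no distance-from-zero measure, so over-correction can count as gain and left and right recoveries can cancel

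*Protocol article*

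**What the plan says.** - **MLBT and MLBT-d.** EWB is the right endpoint weighting minus the left. The section on the MLBT states "Perfect performance would yield symmetrical right and left endpoint weightings of 0.5, and an EWB-value of zero". It sets limits on both sides, +0.09 and -0.13, "leading to upper and lower cut-offs for left and right neglect respectively". The digitized version "is also used as study outcome measure".
- **SLBT.** Each line is scored as (mark - true center)/true center, as a percentage. "The relative deviation scores will then be averaged across all 20 lines to generate the summary score". By this formula an unbiased patient scores zero. The diagnostic rule, more than 10% from the center, gives no direction.
- **BTT.** The score is the mean x-coordinate of the cubes: "An average positive x-coordinate indicates a rightward bias". That zero means no bias follows from this sign convention; the section does not state it.
- **Statistical analyses.** Linear mixed models "will be used to test for change in the primary and secondary outcome measures both within and between group". The covariates are baseline score, time since stroke, gender and age. Lesion side is not among them, and no absolute value or recoding by side is mentioned.
- **Who can enter.** Under Procedure, neglect on one of four screening tasks is enough. Under Active tACS, the small electrode goes over P3 or P4 on the contralesional side, so either lesion side can enrol.
- **Contrast.** CVDT scores are defined as ipsilesional, contralesional and bilateral, so that outcome is already aligned to the lesion.

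**The concern.** A linear model credits every step in one direction equally. On a score whose best value lies in the middle of the scale, that is right only while patients stay on one side of zero. Three situations break it, and the design allows all of them:

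1. A patient with a bias is pushed beyond zero to the other side.
2. A patient who qualified on the bells or balloons task, with normal bisection, is given a bias.
3. Patients with left and right neglect recover in opposite numerical directions, so their changes offset each other in the group mean.

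The first two can produce an apparent benefit where distance from correct performance is unchanged or worse. The third can hide a real benefit. MLBT-d, SLBT and BTT make up three of the six secondary outcomes; the others are CVDT, CBS and SNQ. BTT is also one of the three measures meant to show carry-over to daily life.

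**Working it through.** **The plan's own figures.** The EWB limits follow from the control mean -0.0217 and SD 0.0546:
-0.0217 + 2 × 0.0546 = +0.0875 (stated as +0.09)
-0.0217 - 2 × 0.0546 = -0.1309 (stated as -0.13)
Both reproduce.

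**Signed change against change in distance from zero** (EWB start and end values assumed):

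| Case | Signed change | Change in \|EWB\| |
|---|---|---|
| +0.20 to 0.00, full correction | -0.20 | -0.20 |
| +0.20 to -0.20, over-correction | -0.40 | 0.00 |
| 0.00 to -0.20, new bias beyond the -0.13 limit | -0.20 | +0.20 |
| -0.20 to 0.00, full recovery from right neglect | +0.20 | -0.20 |

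The signed score gives over-correction twice the credit of full correction. It scores a new abnormal bias the same as full correction, and it scores recovery from right neglect as worsening.

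**A patient normal on the task.** Assume active tACS shifts EWB by -0.10 beyond sham.
- P(EWB < -0.13) before the shift: z = (-0.13 + 0.0217)/0.0546 = -1.98, giving 2.4%.
- After the shift the mean is -0.1217: z = (-0.13 + 0.1217)/0.0546 = -0.15, giving 44%.
- Mean |EWB| (folded normal) rises from 0.047 to 0.122.
- With a shift of 0.044 the mean is -0.0657: z = -1.18, giving 12%.

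**At trial level.** Inputs: 11 per arm (Sample size estimates). The rest is assumed: patients normal on the task follow the control distribution, the others have mean 0.20 and SD 0.10, noise SD is 0.05 at each visit, and the shift is the same for everyone in the active arm. The test is a two-sided t-test on change, as a simple stand-in for the mixed model.
- SD of change = 0.05 × √2 = 0.071.
- Shift 0.10: d = 0.10/0.071 = 1.41, and the signed test succeeds in about 88% of trials.
- Shift 0.044 (0.8 × 0.0546): d = 0.044/0.071 = 0.62, and it succeeds in about 28%.

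Neither rate depends on how many patients had a bias to correct. The group difference in |EWB| change does (negative means closer to zero):

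| Share normal on the task | Shift 0.10 | Shift 0.044 |
|---|---|---|
| 25% | -0.045 | -0.024 |
| 50% | -0.008 | -0.009 |
| 75% | +0.027 | +0.005 |

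**Cancellation.** Assume every patient starts at 0.20 from zero, active treatment corrects each one fully, sham does nothing, and noise SD is 0.0546 at each visit. With 10%, 20%, 30% and 50% right neglect, the unaligned signed test detects the benefit in about 81%, 51%, 25% and 3% of trials. The absolute score keeps more than 99% throughout.

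**The case against.** **The article never says that a lower signed score is improvement.** Nor does it say that the raw score enters the model; a fuller analysis plan could transform it. The two-sided EWB limits and the direction-free SLBT rule suggest that the authors regard deviation either way as abnormal. This limits the point, so a reader should not infer that the trial will call over-correction a success. It does not remove the point: the article defines these scores by formula or sign convention and names the model, and the scores it defines are signed. The baseline covariate does not help, because the model still tests a mean shift in one direction.

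**The 0.10 shift is large.** It is 0.10/0.0546 = 1.8 control SDs, applied equally to patients with and without bias. At 0.044 the signed test succeeds far less often, and mean distance from zero changes little in any mix. This stands. The documents give neither the shift nor the share of patients unbiased on bisection.

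**The Background does not show that tACS moves bisection scores.** A reader might infer that alpha tACS pushes any patient to one side. The text says only that it "can be used to influence visuospatial attention performance in healthy participants", and in sub-acute patients, in a single session. It names neither bisection nor the baking tray task, and it says nothing about repeated sessions carrying chronic patients past zero. It makes a directional shift conceivable, no more.

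**Absolute scores have a price.** They are skewed, and zero is not quite the healthy mean (-0.0217). In the 25%-normal case with a 0.10 shift, where distance from zero truly improves, the absolute test detects it in about 23% of trials against 88% for the signed test. This is why the absolute score should sit beside the signed score and not replace it.

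**Loss on the intact side is already visible.** CVDT is scored per side and the star cancellation score is derived for left and right fields, so nothing more is needed there.

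**Conclusion.** The concern holds in a limited form. As written, the analysis of SLBT, MLBT-d and BTT uses signed scores with no alignment to lesion side and no measure of distance from zero. A group difference on such a score therefore cannot by itself be read as less neglect, and a real benefit can be diluted if both lesion sides enrol.

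The arithmetic is certain; the size is not. Under a -0.10 shift the signed test favours active in about 88% of trials, whether mean distance from zero improves by 0.045 or worsens by 0.027. Under a 0.044 shift it does so in about 28%. These figures rest on an assumed shift, patient mix and noise. For BTT, zero as the no-bias value is inferred.

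The primary outcome, quality of search on star cancellation, is higher-is-better and is not affected. A reader might infer that the trial's main conclusion is at risk, but the documents do not support that. The point deserves correction before unblinding, at the level of secondary outcomes.

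**What to change.** In Statistical analyses, for SLBT, MLBT-d and BTT:

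1. Code each score relative to lesion side, as the protocol already does for CVDT, so that the same sign means an ipsilesional bias in every patient. Lesion side is among the baseline descriptors.
2. Analyse change in distance from zero (absolute SLBT summary score, absolute EWB, absolute mean x) alongside change in the aligned signed score.
3. Claim improvement on a task only if distance from zero also falls with active relative to sham. Report the signed result alone as a shift in direction.

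This is a change of wording and needs no new data. The cost is sensitivity: the absolute score is skewed and can have much less power when some patients are unbiased at baseline (about 23% against 88% in the 25%-normal case above). With 11 per arm, some true gains will then be reported only as a directional shift. Settling the rule before unblinding avoids choosing the scoring after the results are known.
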